### Evaluation

Three outcomes will be evaluated: (1) the proportion of participants who make an appointment with a physician following a mobile message reminder, (2) the proportion of participants who keep the appointment, and (3) the proportion of participants who report the results of the screening (via text or Web). To facilitate comparison with existing literature, each outcome will be examined independently as a separate outcome. Adherence rates in the intervention and control group will be compared using the Fisher exact test.

Our second goal is to examine user adoption, identify factors that foster or hinder adoption, and identify patients who are at high risk of nonadherence. Examination of these questions will utilize data from the intervention group only. We hypothesize that those who respond to texts will show higher levels of adherence and patient activation than those who do not respond. For these analyses, we will focus on both user responses to reminders and adherence, which will be treated as a continuous variable by counting the total number of adherence behaviors (eg, made the appointment, kept the appointment, and followed up after results). Factors that foster or hinder adoption will be examined both preintervention and postintervention utilizing all available measures, particularly those related to technology acceptance factors defined in the UTAUT model. Examination of user adoption and factors fostering or hindering adoption will be accomplished through ordinary least-squares regressions. The UTAUT survey questionnaires are designed to measure 4 latent factors that drive technology adoption: performance expectancy, effort expectancy, social influence, and facilitating conditions. The first 3 factors are linked to behavior intention, another latent factor. We will conduct confirmatory analysis using structural equation modeling technique against the data. This will result in a path diagram that weights each latent factor’s contribution to user adoption of this technology. The analysis will help to identify the key drivers of user adoption and give the team directions for further product improvements.

The PAM survey contains 13 questions that measure 4 different aspects of patient activation. We will calculate a mean score and standard deviation for each question in the following groups: intervention, control, intervention who reported outcomes, and intervention who did not report outcomes. We will then detect any significant differences in PAM scores among those groups. A significant difference between intervention and control could indicate that the reminders themselves help activate the patient; a significant difference between the ones who reported outcomes and the ones who do not could provide a signaling mechanism to identify high-risk patients through automated means.

Based upon the patterns of adherence among patients receiving the intervention, it may be possible to identify those patients at highest risk for nonadherence and to identify which variables differentiate those at risk of nonadherence from those who are most likely to adhere.

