## Introduction

Cancer is the second most common cause of death in the United States. In 2012, it is estimated that 1.6 million new cancer cases will be diagnosed and 577,190 Americans will die from cancer [1]. At least half of all new cancer cases can be prevented or detected by screening. Cancer screening not only prevents unnecessary cancer deaths, but it also can reduce the morbidity of cancer before it progresses to more advanced aggressive stages [2]. Despite the benefits of cancer screening, public adherence to guidelines for cancer screening is often poor. *Healthy People 2020*, the 10-year health agenda released by the US Department of Health and Human Services, reported only modest screening rates for breast cancer, cervical cancer, and colorectal cancer. For example, only 59% of adults reported being up-to-date with colorectal cancer screening [3].

Although screening can be beneficial, it is important that patients consult their doctor to determine which types of screening are appropriate for them. Screening guidelines vary widely depending on the type of cancer, patient age, gender, ethnicity, and family history [2]. Patient confusion over multiple recommendations and modalities for cancer screening has been found to be a major barrier to screening adherence [4]. Complicating this matter is the fact that cancer screening schedules often need to be dynamically adjusted for each individual based on previous screening results and comorbidities. For example, the recommended interval between prostate-specific antigen (PSA) tests depends on the most recent PSA level, with longer intervals (ie, less frequent testing) for men with lower PSA levels [5]. Similar dynamic screening and intervention algorithms have been suggested for other types of cancers, such as breast cancer [6,7].

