## Methods

### Study Objectives

Our primary hypothesis is that use of the mobile messaging reminders will increase patient adherence to screening. To evaluate this hypothesis, we will conduct a randomized controlled trial in a sample of males between 40 and 75 years (eligible for prostate cancer screening) who are willing to receive text messages, email, or automated voice messages. The sample will be recruited from male clinic patients who may or may not be in the clinic for prostate-related problems at the time of recruitment.

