### Screening Reminders

A screening schedule reminder will be sent to remind the participant to make an appointment for the screening test. One week after the participant confirms his appointment, the system will ask the participant whether he has seen the doctor yet. This message will repeat every 2 weeks until the participant confirms that he has kept the appointment and seen the physician. Then the system will ask the participant whether he has received his test results. This message will repeat every 3 days until the participant confirms that he has received the test results. The participant will then be asked to report back his test results to the research team using the secure Web portal.

In addition to the messages, we will also provide patient education and health promotion materials to the participants as part of the communication process. Upon initial registration on the secure website, a short video will explain the importance of prostate cancer screening and what to expect from the screening tests to both the control and intervention group participants. Once the intervention group participants confirm and report back their test results, another short video will explain ranges and meanings of test results, and the preventive actions the participant can take to reduce prostate cancer risk.

At the end of the study period, all patients will be contacted again through their preferred communication channels as indicated at sign-up (eg, text message, email, or voice message). All participants will be asked to report whether they have made appointments for prostate screening, kept their appointments, and reported back the test results. All participants will also be asked to complete a second questionnaire on the secure website that is a repeat of all initial questionnaire items except the sociodemographic items. The study period will last 8 weeks. Participants will receive a US $10 gift card as compensation for their participation in this study.

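### No listed outcome is completion of the screening test, so the trial gives indirect rather than direct evidence on its primary hypothesis about screening adherence

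*Protocol article*

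**What the plan says.** Under Study Objectives, the Protocol article states: "Our primary hypothesis is that use of the mobile messaging reminders will increase patient adherence to screening".

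Under Evaluation, it announces three outcomes and examines each separately: "1) the proportion of participants who make an appointment with a physician following a mobile message reminder", then "2) the proportion of participants who keep the appointment, and (3) the proportion of participants who report the results of the screening". The arms are compared by the Fisher exact test.

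Under Screening Reminders, the message about attendance repeats "until the participant confirms that he has kept the appointment and seen the physician". The next step is: "Then the system will ask the participant whether he has received his test results". He is then asked to send the results to the research team. At the end of the 8-week study period, men in both arms are asked whether they booked, attended and reported.

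Under Study Procedures, all men are asked to arrange prostate screening within 3 weeks. Only the intervention arm gets reminders and confirmations, and these cover reporting of results as well as booking and attending.

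**The concern.** The hypothesis concerns screening, and the event that defines screening is the test. Two of the outcomes come before that event and the third comes after it. A man who attends but is not tested counts as a success on outcome 2. A man who is tested but does not report counts as a failure on outcome 3.

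At stake is how a positive result may be read. A rise in kept appointments could be presented as an equal rise in screening. A rise in reported results could come partly or wholly from the prompts to report, which one arm receives and the other does not.

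**Working it through.** **Step 1: set the outcomes against the event of interest.** The sequence is: book, attend, be tested, receive the result, report it.

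| Measure | Place in the sequence | What it says about testing |
|---|---|---|
| Outcome 1, booked | before the test | intention only |
| Outcome 2, attended | before or at the test | close proxy if nearly every kept visit includes the test |
| Outcome 3, reported | after the test | a report implies a test; no report leaves it unknown |
| End-of-study questions, both arms | same three behaviours | no stated question on whether the test was done |

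The message flow passes from having seen the physician directly to having received results. The adherence count in the intervention-only analysis (Evaluation) gives booking, attending and follow-up after results as its examples, and the test is not among them.

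**Step 2: outcome 2 as a proxy.** The article gives no expected rates, sample size or power, so there is no figure to reproduce. Every rate below is an assumption chosen to show the mechanism.

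P(tested) = P(kept) × P(tested | kept). Take kept visits of 45% (intervention) and 30% (control), a 15-point gain. With c1 and c0 as the shares of kept visits that include a test in the intervention and control arms, the gain in tests is 0.45·c1 − 0.30·c0.

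| c1 | c0 | Gain in tests done |
|---|---|---|
| 0.90 | 0.90 | 0.405 − 0.270 = 13.5 points |
| 0.70 | 0.70 | 0.315 − 0.210 = 10.5 points |
| 0.65 | 0.80 | 0.2925 − 0.240 = 5.3 points |
| 0.60 | 0.80 | 0.270 − 0.240 = 3.0 points |

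With equal conversion the difference shrinks modestly and the ratio stays at 0.45/0.30 = 1.5. The large losses need lower conversion in the reminder arm.

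**Step 3: outcome 3 as a proxy.** P(outcome 3) = P(tested) × P(reports | tested). Hold testing equal in both arms and let reporting differ, as it might when one arm is prompted.

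| Tested, both arms | Reporting, control / intervention | Outcome 3, control / intervention | Difference |
|---|---|---|---|
| 30% | 40% / 60% | 12% / 18% | 6 points |
| 50% | 40% / 60% | 20% / 30% | 10 points |
| 70% | 40% / 60% | 28% / 42% | 14 points |
| 30% | 30% / 80% | 9% / 24% | 15 points |
| 50% | 30% / 80% | 15% / 40% | 25 points |
| 70% | 30% / 80% | 21% / 56% | 35 points |

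With an assumed 100 men per arm, the 15% versus 40% case would reach two-sided significance at 0.05 with probability about 0.98 (normal approximation), with no difference in screening.

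The reverse can also occur. With testing of 30% (control) versus 50% (intervention) and reporting of 80% versus 48%, outcome 3 is 0.30 × 0.80 = 24% and 0.50 × 0.48 = 24%, which hides a real 20-point gain.

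**The case against.** The strongest reply is that the counted appointment is not a general visit. Study Procedures asks men to arrange prostate screening, and Screening Reminders ties both the reminder and the end-of-study question to a screening appointment. Keeping it should usually mean being tested. This stands, and it makes outcome 2 a reasonable proxy.

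Outcome 3 also carries direct information, because a man with a result to report has been tested. That stands for reporters. It does not cover non-reporters, or the difference in prompting between arms.

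All men repeat the initial questionnaire apart from its sociodemographic items, and the initial set includes health history. An item on recent PSA testing is therefore possible. The article does not say there is one and names no outcome based on it; the full questionnaire might settle this.

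Three stronger readings are tempting and are not supported:

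- A reader might infer that the trial says nothing about screening uptake. It does not follow, because outcomes 2 and 3 are both informative, though indirectly.
- A reader might infer that many kept visits would end without a test because the men recruited "may or may not be in the clinic for prostate-related problems". That sentence describes the visit at which a man is recruited, not the later screening appointment.
- A reader might take the Introduction's remark that "it is important that patients consult their doctor to determine which types of screening are appropriate for them" as a description of the trial visit. It is general background on cancer screening and says nothing about how often the trial appointment ends in a test.

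Finally, the choice of booking, attending and reporting is consistent with the article's own list of adherence behaviours, so this is not an internal contradiction. It is a gap between the stated hypothesis and what is measured.

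**Conclusion.** The point holds in a limited form. The stated outcomes and end-of-study questions do not include test completion, and no listed outcome measures it evenly across arms. The trial as described gives indirect evidence on screening uptake. Outcome 2 is a fair proxy whose error depends on the unknown share of kept visits that include a test. Outcome 3 is the weaker proxy, because it combines testing with reporting that is prompted in one arm only.

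The size of either error cannot be derived from the article. The ranges above (a true gain of 3 to 13.5 points behind a 15-point gain in kept visits; a spurious 6 to 35 points on outcome 3) rest wholly on assumed rates. In particular, nothing in the article shows that reminders draw in men less likely to be tested, so the 3- and 5.3-point cases show what is possible, not what is expected.

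This is not a matter that an analysis plan could settle later. The article presents the outcome list as complete, and an item that is not collected cannot be analysed. If the repeated health-history items already record testing during the study, what remains is to name that item as an outcome.

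**What to change.** Add one item to the end-of-study contact that both arms already receive: was the screening test done since sign-up, and on what date. Define test done within the 8-week study period, among all randomised men, as the outcome that answers the primary hypothesis, and compare the arms with the Fisher exact test already planned. Keep booking, attending and reporting as process outcomes. State one rule, the same in both arms, for men who do not answer.

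The cost is one more self-reported question. The headline effect may be smaller than the effect on kept appointments. The item remains self-report, but it is asked once and in the same way in both arms.

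Confirmation from clinic records is optional and should not be a condition of the fix. Recruitment covers 3 clinics and 2 community health fairs (Eligibility Criteria). A check at the designated clinics would not cover the health-fair recruits, would mix methods of ascertainment, and would add record access at the sites. If it is done, it should be done alike in both arms and used as a supporting check.

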In this project, we propose to develop technology-based interventions, specifically, automated reminders sent to consumer mobile phones to help patients stay motivated and adherent with their personalized cancer screening schedules. The interventions are based on the theory of planned behavior [19], in particular the unified theory of acceptance and use of technology (UTAUT) [20] and the Patient Activation Measure (PAM) [21]. The UTAUT is a theoretical model and instrument used to assess the likelihood of user acceptance for new technology that posits that performance expectancy, effort expectancy, social influence, and facilitating conditions are direct determinants of use [20]. The UTAUT instrument is widely used to evaluate the factors affecting adoption of new technology solutions [22]. Patient activation refers to a person’s ability and willingness to manage their health and health care [23]. The PAM is a 22-item assessment used to evaluate an individual’s knowledge, beliefs, and confidence in managing their health [21]. High patient activation has been shown to be positively associated with utilization of preventive services, self-management behaviors, medication adherence, self-reported quality of care, and perceived doctor-patient communication [24-26].

We will conduct a randomized controlled trial to study the hypothesis that mobile reminders improve adherence to screening guidelines. Mobile messaging is an intervention that can be applied to a large population at low cost because it can be easily automated. We will also explore a secondary hypothesis that patients who reply to the messaging reminders are more engaged and at lower risk of nonadherence. The impact is that low-cost mobile messaging could be used as a signaling mechanism to predict patients with high risk of nonadherence, and resources could be optimized to target those patients for more intensive follow-ups.

In this project, we focus on prostate cancer to examine proof of principle for our general approach. We will use screening algorithms adapted from evidence-based prostate screening guidelines and multimedia content tailored for mobile phone use. We plan to subsequently develop and test algorithms for other types of common cancers, such as breast cancer and colorectal cancer.

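### In the intervention-arm analysis of replies against adherence, both are recorded through the same messages, so men who do not reply are under-recorded and the association cannot by itself show that silence signals nonadherence

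*Protocol article*

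**What the plan says.** The secondary hypothesis is in the Evaluation section of the protocol article: "We hypothesize that those who respond to texts will show higher levels of adherence and patient activation than those who do not respond". The population is restricted: "Examination of these questions will utilize data from the intervention group only". Adherence enters as a score obtained by "counting the total number of adherence behaviors (eg, made the appointment, kept the appointment, and followed up after results", and is handled as continuous. The third trial outcome in the same section is "the proportion of participants who report the results of the screening (via text or Web".

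The Screening Reminders section shows how these steps become known in the intervention arm. After the booking reminder, "One week after the participant confirms his appointment, the system will ask the participant whether he has seen the doctor yet". Then, "This message will repeat every 2 weeks until the participant confirms that he has kept the appointment and seen the physician". Only after that does the system ask about test results, and only after receipt is confirmed is the man asked to report them.

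The same section describes a second source. At the end of the 8-week study period every participant, in both arms, is asked whether he booked, attended and reported results. This contact goes out on the channel he chose at sign-up.

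The Introduction gives the intended use: "low-cost mobile messaging could be used as a signaling mechanism to predict patients with high risk of nonadherence", so that intensive follow-up can be directed to those men.

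**The concern.** The predictor is whether a man responds to messages. The outcome is a score that the investigators fill in, during follow-up, largely from those responses. Three features tie the two together.

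- Booking and attendance are learned from his confirmations.
- The prompts are chained. A man who does not confirm one step is not asked about the next, so he has fewer chances both to respond and to have a behaviour recorded.
- Reporting results is a response to the system in its own right.

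Silence and nonadherence then look alike in the data. A man who was screened but ignored the messages can be recorded like a man who never booked. If the trial reports that non-responders adhere less and recommends targeting them, the recommendation may rest on how adherence was recorded and not on what the men did.

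**Working it through.** **Nothing to reproduce.** The article gives no sample size, adherence rate, reply rate or week-8 response rate for this analysis. It also does not say how a man with no report is scored. Every rate below is an assumption, used only to show the range.

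**Step 1: sources for each counted behaviour in a reminder non-replier.**

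| Behaviour | During follow-up | At week 8 |
|---|---|---|
| Booked | not confirmed | known only if he answers |
| Attended | not asked, because booking was not confirmed | known only if he answers |
| Reported results | not asked; reporting is itself a reply | known only if he answers |

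The article names no source that works without a reply. The third item of the score is worded as following up after results. It is read here as the third trial outcome, because reporting is the only participant step after results that the article describes.

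**Step 2: the gap if silence is scored zero.** Let true adherence be the same in repliers and non-repliers, with mean count M, and let q be the share of reminder non-repliers who answer at week 8. Repliers are recorded at M on average and non-repliers at q × M. The spurious gap is M − qM = (1 − q) × M.

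Assume true rates for the three behaviours of 0.6/0.5/0.4 (M = 1.5) or 0.4/0.3/0.2 (M = 0.9), with 70% of men replying. A simulation of 4000 trials per setting used a two-group t test at two-sided 0.05, which is equivalent to least squares on a reply indicator.

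| q | Gap, M = 1.5 | False positives, 50 / 100 men | Gap, M = 0.9 | False positives, 50 / 100 men |
|---|---|---|---|---|
| 0 | 1.50 | 100% / 100% | 0.90 | 94% / 100% |
| 0.25 | 1.125 | 80% / 99% | 0.675 | 51% / 83% |
| 0.50 | 0.75 | 43% / 72% | 0.45 | 22% / 41% |
| 0.75 | 0.375 | 15% / 23% | 0.225 | 8% / 12% |
| 1 | 0 | 5% / 4% | 0 | 5% / 5% |

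At q = 1 the test returns to its nominal level, so the excess comes from recording alone. In these runs 40% of repliers (M = 1.5) or 60% (M = 0.9) had a score of zero, so the bias arises from what is not recorded for non-repliers.

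**Step 3: the gap if silence is treated as missing.** Under the same model, non-repliers who answer at week 8 have expected mean M, as repliers do, so the expected gap is M − M = 0. The bias therefore depends on two things the article does not state: q and the scoring of silence.

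**Step 4: result reporting.** Step 2 lets the week-8 contact recover the third item like the others. If reminder non-repliers, who are never prompted to report, in fact do not report, that item adds a gap equal to its rate in repliers even when q = 1: at most 0.4 or 0.2 under the assumed rates. Unprompted reporting on the website would reduce this.

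**Step 5: number of replies as predictor.** The article does not fix how response is measured. With chained prompts, adherent men get more prompts to answer. Assume true rates of 50/40/30% and each prompt answered half the time regardless of adherence. Regressing the true count, fully captured, on the number of replies then rejected in about 31% of trials with 50 men and 55% with 100. A predictor tied to the first reminder, which every intervention man is due to receive, avoids this.

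**The case against.** A reader might infer that men who reply are adherent by construction, or that the regression is bound to confirm the hypothesis. The document supports neither. The system asks whether the man has seen the doctor, so a negative answer is a reply. The week-8 contact asks all men about booking and attendance, so it can recover adherence in men who ignored reminders. At 75% recovery the simulated false-positive rate is 8% to 23%, far from certain confirmation.

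It can also be said that the tabulated gaps rest on scoring silence as zero, which the article nowhere states, and that missing-data handling is commonly left to a fuller document. That stands, and it is why no single size is claimed. Enrolment requires a confirming reply on the chosen channel, so the article gives no support for assuming that recovery is low. Figure 1 is not shown and the article may condense a fuller protocol, so a record check cannot be excluded.

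The patient-activation half of the hypothesis uses the PAM, first completed before any reminder, and is not circular in this way. The repeat PAM does require the man to respond.

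It is also tempting to fault least squares on a 0–3 score. The article assigns that method to adoption and the factors behind it, and does not name the test for responders against non-responders. An ordinal model would be a preference and would leave the recording problem untouched.

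What remains is the shared channel. The week-8 contact needs another reply on the same channel, and reporting results overlaps with replying by definition.

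**Conclusion.** The point holds in limited form. Relating replies to this adherence count builds in some association, because reminder non-repliers are under-recorded or missing unless they answer at week 8, and because one counted behaviour is a reply. Such an association cannot on its own support using silence to identify men at risk of nonadherence.

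The size cannot be fixed from the document. If silence is scored zero and replying is unrelated to true adherence, the gap is (1 − q) × M, which under the assumed rates runs from 0 at full recovery to 1.5 behaviours at none. If silence is treated as missing, the same model gives no expected gap on booking and attendance, and only the result-reporting overlap remains.

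The analysis is secondary and the article describes it as exploratory. The point does not bear on the randomised Fisher comparison or on baseline PAM. It matters because the article attaches a practical use to the result.

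**What to change.** For this analysis only:

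1. **Predictor.** Any reply to the first screening reminder, including no or not yet, within a fixed window (7 days, for example).
2. **Outcome.** Booked and attended, scored 0–2, taken from the week-8 contact that puts the same questions to all men. Leave result reporting out of the score.
3. **Silence at week 8.** Treat as missing in the main analysis, with a sensitivity analysis that scores it as nonadherent. The latter carries the artefact in full. With assumed rates of 0.6 and 0.5 and q = 0.5 it adds (1 − 0.5) × (0.6 + 0.5) = 0.55, so it serves as an extreme case and not as confirmation.
4. **Reporting.** Give week-8 response separately for first-reminder repliers and non-repliers, so that readers can judge q.

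The change is to analysis wording and uses contacts already planned. Costs: late first replies count as non-response, and confirmations made during the study are not used here. Some dependence on replying at week 8 also remains, and should be stated as a limit on the conclusion. Checking clinic records would remove that dependence, but the article does not provide for it; it would be new data collection across three clinics and two health fairs, so it is an option and not part of this change.

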### Study Procedures

After initial recruitment, participants will be asked to complete a brief questionnaire about their basic sociodemographic details and relevant health history, as well as a Technology Acceptance Model questionnaire [22] and the PAM [21] to measure patient engagement in health care. Participants will be randomly assigned to the intervention or the control group using a random number generator. Randomization will be implemented automatically by a secure password-protected algorithm at the time the user signs up. This guarantees that assignment cannot be predicted before or changed after the participant is registered in the study. All participants will be asked to schedule prostate cancer screening at the clinic within the next 3 weeks, but only the intervention group will receive reminders and confirmation communications for (1) making an appointment, (2) keeping the appointment, and (3) reporting test results back to the investigators.

A flowchart of the reminders/confirmations and the expected responses from participants is illustrated in Figure 1.

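### The planned PAM comparison between arms can show an effect of reminders plus the results video, not of the reminders alone, and the reporter comparison should rest on baseline PAM

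*Protocol article*

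**What the plan says.** All references are to the protocol article.

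- **Reminders (Study Procedures).** They go to one arm: "only the intervention group will receive reminders and confirmation communications".
- **First video (Screening Reminders).** It is shown at registration "to both the control and intervention group participants", so it is balanced.
- **Second video (Screening Reminders).** It is described for one subgroup: "Once the intervention group participants confirm and report back their test results, another short video will explain ranges and meanings of test results". It also covers "the preventive actions the participant can take to reduce prostate cancer risk". No such video is described for controls.
- **PAM measurement.** At entry, men complete a short questionnaire "as well as a Technology Acceptance Model questionnaire [22] and the PAM [21] to measure patient engagement in health care" (Study Procedures). All items except the sociodemographic ones are repeated in both arms at the end of the 8-week study (Screening Reminders).
- **PAM analysis (Evaluation).** Scores are summarised in four overlapping groups: intervention, control, intervention reporters and intervention non-reporters. Two readings are attached. For the arms: "A significant difference between intervention and control could indicate that the reminders themselves help activate the patient". For reporters against non-reporters: "a significant difference between the ones who reported outcomes and the ones who do not could provide a signaling mechanism" for finding high-risk men automatically. The paragraph does not say whether baseline, end-of-study or change scores are meant.

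**The concern.** The Introduction describes PAM as a measure of what a person knows and believes about looking after his health, and how confident he is in doing so. A video that explains a man's results and what he can do to lower his risk works on the same ground. It is given in one arm only, and within that arm only after the man has reported. It is therefore tied both to the randomised contrast and to the reporter contrast.

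Two interpretations are at stake. One is that the reminders, with nothing else, activate patients. The other is that reporting behaviour marks out poorly activated men. The Introduction would use the second to direct more intensive follow-up, so a gap partly created by the video could lead the team to trust the flag more than it deserves.

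**Working it through.** The plan gives no PAM effect size, standard deviation or reporting rate, so there is no figure of its own to reproduce. The check is mainly a comparison of who receives what, and when.

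**Step 1: exposure by group at each PAM measurement**

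| Group | Baseline PAM | End-of-study PAM |
|---|---|---|
| Control | No reminders, no second video | No reminders, no second video described |
| Intervention, did not report | No reminders, no second video | Reminders, no second video |
| Intervention, reported | No reminders, no second video | Reminders, plus second video if he reported before answering |

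**Step 2: intervention against control.** Randomised arms differ at baseline only by chance, so evidence that the intervention activates patients must come from end-of-study or change scores. In that column the arms differ in two components. Randomisation supports a causal statement about both together. The planned contrast cannot divide the effect between them.

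**Step 3: reporters against non-reporters.** In the end-of-study column, having reported and having been offered the video coincide, except for late reporters. A higher score in reporters could mean that they were more activated to begin with, that the video raised their score, or both. In the baseline column neither group has seen the video, so it contributes nothing to the gap.

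**Step 4: illustration of size.** Let *r* be the share of intervention men who see the second video before the final questionnaire, and *v* the video's effect on PAM in SD units. Suppose the reminders have no effect on PAM.

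- Expected between-arm difference at the end of study = *r* × *v*.
- Contribution of the video to the end-of-study reporter gap = at most *v*, reached if every reporter saw it in time.
- Contribution of the video to either contrast at baseline = 0.

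The documents give neither *r* nor *v*. The following ranges are assumptions: *r* = 0.2 to 0.6, *v* = 0.2 to 0.5 SD.

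- Low end between arms: 0.2 × 0.2 = 0.04 SD.
- Middle effect, *v* = 0.3: 0.2 × 0.3 = 0.06 SD to 0.6 × 0.3 = 0.18 SD.
- High end between arms: 0.6 × 0.5 = 0.30 SD.
- Reporter gap at the end of study: up to 0.2 to 0.5 SD from the video alone.

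The between-arm share is diluted because only reporters are offered the video. The reporter contrast has no such dilution, which is why the choice of time point matters more there.

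**The case against.** **The wording is hedged and the analysis exploratory.** Both sentences say only what a difference could mean, and the educational material is presented as part of the communication process, so the video may be regarded as belonging to the tested intervention. The second part of this supports the package reading. The hedge does not rescue the sentence, because it singles out the reminders and the planned contrast cannot do so.

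**A reader might infer that PAM cannot serve as a risk signal at all.** The documents do not support that. The Evaluation section fixes no time point, and PAM is collected at baseline before any second video. The Introduction and Evaluation are also more naturally read with replying or reporting as the automated flag and PAM as the trait against which it is checked. The concern that remains is conditional: if end-of-study scores are used, the video may flatter the flag.

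**A reader might assume that every reporter sees the video before the final questionnaire.** The article does not guarantee that order. A man who reports late may answer first, and nothing shows how many watch it. Men are asked to schedule screening within 3 weeks of an 8-week study, so earlier reporting is the expected sequence, but not a certain one.

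**A reader might extend the point to technology acceptance**, since "Factors that foster or hinder adoption will be examined both preintervention and postintervention utilizing all available measures". That is a separate matter. It does not depend on the video, and preintervention measures are already included.

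**The video is short and specific to prostate cancer, while PAM is general.** Its effect may therefore be small. This stands, and the documents cannot settle it.

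**Conclusion.** The point holds in a limited form. A between-arm difference in end-of-study or change PAM would be evidence for the messaging package (reminders plus results video). It would not be evidence for the reminders alone. A reporter against non-reporter difference in end-of-study PAM could be partly a consequence of reporting; the same comparison on baseline PAM would be free of the video.

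The size of the bias cannot be found from the documents. The 0.04 to 0.30 SD between arms, and up to 0.2 to 0.5 SD between reporters and non-reporters, rest wholly on assumed values of *r* and *v* and show only what could happen. The conclusion itself does not need them: it rests on the second video being described for one arm only and triggered by reporting.

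Appointment-making, appointment-keeping and reporting of results all precede the video, so those three outcomes are unaffected.

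**What to change.** Two changes to the PAM paragraph in the Evaluation section:

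1. State that a between-arm difference in PAM would be attributed to the messaging package, meaning the reminders together with the results video, and delete the attribution to the reminders alone.
2. State that the reporter against non-reporter comparison, when used for the risk signal, is based on baseline PAM. End-of-study scores in these two groups may still be shown, described as possible consequences of reporting.

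Both are wording changes that use data already planned, with no added burden for participants. The cost is a narrower claim about the reminders. The second video need not be shown to other men or at another time, since the package conclusion is sound with the design as it stands.
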